**Hypotheses:**

We hypothesize that colonic SCFAs delivery will modulate neuroendocrine, cardiovascular, and subjective responses to an acute laboratory psychosocial stress task. As secondary outcome measures, we will assess alterations in restrictive eating behavior and nutritional status, as reflected by changes in body mass index. Additionally, we will explore changes in microbiota composition, gastrointestinal symptoms, eating disorder psychopathology, and related comorbidities.

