Short-chain fatty acids (SCFAs), metabolites produced following the bacterial fermentation of dietary fiber in the large intestine, are considered candidate mediators of the gut bacteria's effects on the host [17]. Acetate, propionate, and butyrate are the most abundant SCFAs and may affect the host through immune, endocrine, neural, and humoral pathways [18]. Stress is the physiological response to a challenging physical, emotional, or cognitive encounter that exceeds the body's coping resources and activates the sympatho-adrenal medullary pathway (SAM) and the hypothalamus–pituitary–adrenal (HPA) axis. Interestingly, recent evidence suggests that SCFAs mediate the effects of gut bacteria on stress responses of the HPA axis [19–21]. Oral supplementation of SCFAs in rodents reduced corticosteroid response to acute stress, reduced stress-induced gastrointestinal permeability, and reversed changes in anhedonia [20, 21]. Human translational research found that administering SCFAs to the large intestine attenuated the cortisol response to acute psychosocial stress [19]. While the stress response can be adaptive and beneficial, prolonged or exaggerated stress can heighten the risk of developing neuropsychiatric disorders [22]. The involvement of the HPA axis in individuals with AN has been implicated in the development and perpetuation of this disorder [23–26]. Researchers hypothesize that eating disorder-related behaviors, such as restricting, binging, purging, or excessive physical exercise, may function as dysfunctional adaptations to alleviate and manage negative affective states [27–29]. These maladaptive eating behaviors often increase in response to stress and negative emotions [30, 31]. This consequently forms a vicious cycle, where the continued physiological state of nutritional deprivation can lead to subjective and objective stress activation (e.g., via chronic HPA axis stimulation and autonomic nervous system alterations) [23, 32, 33]. The possible role that the gut microbiota and SCFAs might play in the maladaptive stress responses and related eating behaviors characteristic of AN is intriguing and presents a promising research avenue to expand our understanding of this complex disorder.

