#### Trier social stress test (TSST)

During the baseline and post-intervention visits, participants will complete the TSST, a widely used standardized psychophysiological stress paradigm. The TSST specifically targets social-evaluative threat and perceived control, initiating a robust acute stress response that activates the sympathetic nervous system and adrenocortical stress response [44]. No significant habituation or sensitization has been found when there is a large enough interval between sequential TSSTs within a subject [45, 46]. Slight modifications are made to the speech and arithmetic part of the task to make it less predictable during the second administration.

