## Outcomes

### Primary and secondary outcomes

The primary outcome of this study focuses on the salivary cortisol response to acute laboratory stress. We will examine the change in cortisol levels within and between SCFAs and placebo groups. Crucial secondary outcomes encompass the participants' food choices and nutritional status (BMI). All other measures delineated in the subsequent sections serve as secondary outcome measures. See Table 1 for an overview of scheduled assessments.

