### Statistical analysis

#### Statistical methods for primary and secondary outcomes

The primary and secondary outcome variables will be analyzed using linear mixed models with “group” (placebo or SCFAs) as a between-subject factor and “visit” (pre- or postintervention) and, where appropriate, “timepoint” (measurement point within each visit) as within-subject factors. The group-by-visit and the group-by-visit-by-timepoint interaction effects constitute the principal effects of interest. If participants fail to exhibit an elevated cortisol stress response following stress induction, we will exclude their data from the analysis. To investigate the effect of the SCFAs intervention on treatment response, we will further control for BMI by including changes in BMI between visits 1, 2, and 3 in the linear mixed model as a continuous covariate. To investigate whether the changes in circulating SCFAs levels are mediated by the changes in the cortisol stress response to our stressor, we will pool all stress responders and enter the change in SCFA levels (post-intervention—pre-intervention) into the linear mixed model as a continuous covariate, including its interaction with visit, while omitting the group variable. The chosen significance level is alpha = 0.05. Follow-up planned contrasts will be conducted if there is a significant interaction effect and will be corrected for multiple testing comparisons using step-down Bonferroni (Holm) adjustment. Data of the intervention group will be further exploratively analyzed using linear mixed models with restrictive type AN and binge/purge type AN as “patient group,” investigating differences between the intervention of SCFAs between subtypes of patients with AN. In addition, we will enter the changes in questionnaires (baseline, post-intervention) into a linear mixed model as continuous covariates to investigate in an explorative way whether these changes (e.g., in AN severity, affect changes, subjective stress, etc.) are mediated by the changes in SCFAs levels and microbiota composition.

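### The exclusion of cortisol non-responders selects on the primary outcome and is not confined to the pre-intervention stress test, so it can make inclusion depend on treatment

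*Protocol article*

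**What the plan says.** Under Primary and secondary outcomes, the protocol article says: "The primary outcome of this study focuses on the salivary cortisol response to acute laboratory stress". On when the response is measured, the section on the Trier social stress test (TSST) says: "During the baseline and post-intervention visits, participants will complete the TSST".

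Under Statistical methods for primary and secondary outcomes, the model is a linear mixed model with group, visit and, where appropriate, timepoint. The target is defined as follows: "The group-by-visit and the group-by-visit-by-timepoint interaction effects constitute the principal effects of interest". The next sentence reads: "If participants fail to exhibit an elevated cortisol stress response following stress induction, we will exclude their data from the analysis". It gives no visit and no threshold, and it does not say whether failing once is enough. No analysis of all randomised participants is mentioned beside it. Responder status is used again further on: "we will pool all stress responders and enter the change in SCFA levels".

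On the expected direction, the Background reports that in earlier human work "administering SCFAs to the large intestine attenuated the cortisol response to acute psychosocial stress". The Sample size section is built on detecting that effect. It plans 40 per arm and raises 80 to 92 for a 15% dropout risk.

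**The concern.** The variable that decides who stays in the analysis is the variable being analysed, and half of its measurements are taken after treatment. If SCFAs lower the cortisol response, as in the earlier study, some treated patients will fall below whatever counts as elevated because of the treatment. If those patients are removed, the arms lose different numbers and different kinds of patients, and randomisation no longer protects the comparison. Blinding the analysts does not help, because the selection works through the outcome and needs no knowledge of allocation.

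At stake are the size of the primary effect estimate, its power, and the number analysed. The sample size holds no reserve for these exclusions.

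**Working it through.** **1. The plan's own power figure.** Inputs from the Sample size section: N = 80, two visits (m = 2), Cohen's f = 0.16. The analysis section adds: "The chosen significance level is alpha = 0.05". The pre/post correlation ρ is not stated. For the within-between interaction, λ = f²·N·m/(1−ρ), with 1 and 78 degrees of freedom. With ρ = 0.5, λ = 0.0256 × 80 × 2/0.5 = 8.19 and power is 0.807, so the stated 80% is reproduced. With ρ = 0.3 power would be 0.666 and with ρ = 0.7 it would be 0.954, so 0.5 is the value to carry forward. Recruitment reproduces as 80 × 1.15 = 92.

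**2. The implied effect.** In a 2 × 2 interaction the cell effects are ±δ/4, so δ = 4 × 0.16 = 0.64 SD difference in change. Check: the variance of change is 2(1−ρ) = 1, and δ² × 40/2 = 0.4096 × 20 = 8.19, the same λ.

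**3. Assumptions not in the document.** Responses are normal with SD 1 at each visit. SCFAs lower the post-intervention response by a constant 0.64 SD. A share p of untreated patients respond (60–90%), so the response threshold is c = Φ⁻¹(1−p). Excluded patients are removed entirely.

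**4. One case by hand: p = 0.70, exclusion on the post-intervention response.** c = −0.524. Placebo keeps 70%. SCFA keeps 1 − Φ(−0.524 + 0.64) = 1 − Φ(0.116) = 45%. Write h(x) = φ(x)/(1−Φ(x)).

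- Placebo mean change among those kept: (1−ρ)·h(c) = 0.5 × 0.497 = 0.248.
- SCFA mean change among those kept: (1−ρ)·h(c+δ) − δ = 0.5 × 0.873 − 0.64 = −0.204.
- Difference: 0.248 + 0.204 = 0.452. Ratio to the truth: 0.452/0.64 = 0.71.
- Number analysed: 40 × (0.70 + 0.45) ≈ 46. Power (noncentral t on change scores): 0.35.

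**5. All readings of the rule.** The same calculation, integrated numerically over the bivariate normal, gives the estimate as a ratio to the truth, then power:

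| Who is excluded | p = 0.60 | p = 0.70 | p = 0.80 | p = 0.90 |
|---|---|---|---|---|
| Nobody | 1.00; 0.81 | 1.00; 0.81 | 1.00; 0.81 | 1.00; 0.81 |
| Non-responders at baseline only | 1.00; 0.65 | 1.00; 0.71 | 1.00; 0.76 | 1.00; 0.79 |
| Non-responders at post-intervention | 0.68; 0.28 | 0.71; 0.35 | 0.75; 0.45 | 0.81; 0.58 |
| Non-responders at either visit | 0.58; 0.22 | 0.63; 0.31 | 0.70; 0.42 | 0.78; 0.57 |
| Only those failing at both visits | 1.20; 0.76 | 1.14; 0.78 | 1.08; 0.80 | 1.04; 0.81 |

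The baseline-only rule analyses 48 to 72 patients, against the 80 on which the power figure rests.

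**6. Other shapes of effect (p = 0.70).** If SCFAs instead cut a skewed response by 40%, with ρ from 0.3 to 0.9, the post-intervention rule gives ratios of 0.58–0.94 on the log scale and 0.92–1.60 on the raw scale. If SCFAs raise the response by 0.64 SD, the post-intervention rule gives 0.79. If SCFAs have no effect, every rule gives a difference of about 0.

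**The case against.** The sentence names no visit. If responder status is judged only before treatment, exclusions are equal between arms in expectation and the ratio is 1.00. Silence on the visit does not show that treated patients will be deleted. This stands, and it is why the point is conditional.

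A reader might go further and infer that the rule drops the patients in whom SCFAs work best, biases the effect toward zero, and will likely make an effective intervention look null. The document does not support that as a flat statement. The hypothesis has no direction: "We hypothesize that colonic SCFAs delivery will modulate neuroendocrine, cardiovascular, and subjective responses to an acute laboratory psychosocial stress task". The sample-size section says there is no information on this effect in anorexia nervosa. The earlier study reports an attenuated response, not an abolished one, and no threshold is given. The direction itself reverses if only patients failing at both visits are dropped, and can reverse for a proportional effect on the raw scale. No inflation of false positives is shown either, since without a treatment effect both arms are selected alike.

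The figures also simplify. They use one response value per visit and a t-test on change, where the plan has a mixed model with timepoints. Excluding a participant's data might mean only the failed visit. That would weaken the numbers but not cure the problem, because the missing post-intervention values would still be missing on account of their own size.

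Finally, an article may leave threshold, visit and analysis sets to the full protocol. Their absence is not faulted here. What is faulted is the rule the article does state, which as worded permits exclusion on a post-treatment value of the primary outcome.

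**Conclusion.** The concern holds in conditional form. The exclusion uses the primary outcome and is not limited to the pre-intervention test. Of the four exclusion readings examined, only baseline-only avoids selection by treatment.

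If the post-intervention response counts, the distortion is most likely toward zero: about 0.58–0.81 of the true effect, with power of 0.22–0.58 instead of 0.81. It is away from zero, about 1.04–1.20, if only those failing at both visits are dropped. Baseline-only exclusion costs power alone (0.65–0.79) under a constant shift, and estimates the effect in a narrower population.

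These sizes rest on 10–40% untreated non-response, correlation 0.5, normal responses and a constant shift of 0.64 SD; only the shift derives from the plan's figures. Confidence is high that the rule as worded allows treatment-dependent exclusion, and lower on the direction and size of the bias. Because the rule acts on the primary comparison and is cheap to repair, it should be corrected before unblinding.

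**What to change.** Remove the exclusion from the primary analysis. State that it includes all randomised participants with cortisol data, in their allocated arm, whatever the size of the response. If a responder analysis is wanted, keep it as a sensitivity analysis, with responder status defined only on the baseline (pre-intervention) TSST and a threshold fixed in advance.

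Confining the existing exclusion to the baseline test would also remove the selection by treatment. It would, however, leave the primary analysis short of patients for whom the sample size made no allowance, so the full set is preferable.

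The model on change in SCFA levels omits group, so no randomised contrast is at risk there. Using the same baseline definition of responder would simply keep the two analyses consistent.

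The cost is a sentence or two, with no new data or patients. The downside is that the average cortisol response will be slightly smaller, because non-reactors stay in.

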### Study aims

Building on the current gaps in the literature, we designed a triple-blind, randomized, placebo-controlled trial to examine the role of SCFAs as mediators of microbiota-gut-brain interactions in AN. Specifically, we aim to assess the effects of SCFAs on the acute stress response, eating behavior, and nutritional status in patients with AN following SCFA delivery to the large intestine using pH-dependent colon-delivery capsules (CDCs). This method allows the administration of SCFAs in exact amounts in a chronically tolerable manner while mimicking, as closely as possible, the process of bacterial fermentation of dietary fiber in the gut. We hypothesize that colonic SCFA administration daily for six weeks will modulate neuroendocrine [cortisol, adrenocorticotropin hormone (ACTH), salivary-alpha amylase], cardiovascular (heart rate, heart rate variability), and emotional responses (subjective stress, anxiety, perceived control, hunger and desire to eat) to acute laboratory stress. Additionally, we predict that the intervention will result in a shift in dietary choices towards less restricted choices, as captured during a food choice task (FCT), and an improvement in the nutritional state, reflected by a greater increase in BMI.

The longitudinal design of this study provides a unique opportunity to examine the causal role of SCFAs in stress and eating behaviors in individuals with AN. By stepping away from the typical cross-sectional studies in the gut microbiota research field, our work can yield new insights into the complex interplay between the gut, stress system, and eating behavior and facilitate new therapeutic targets for stress-related psychiatric disorders.

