### Study design and setting

This study is a monocentric, randomized, triple-blind, placebo-controlled trial with two parallel arms. Participants in both groups will receive concomitant treatment as usual, consisting of an inpatient psychotherapeutic program of 12 weeks focusing on nutritional rehabilitation. Using a block randomization method, we will randomly assign participants to the placebo or SCFA group with a 1:1 allocation ratio. The total duration of the study is 12 weeks, including a pre-intervention baseline visit, which takes place within the first week of hospitalization, a post-intervention visit at six weeks, and a follow-up visit at 12 weeks. The study will be conducted at the Leuven University Psychiatric Hospital (UPC Z.Org), Belgium.

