#### Follow-up visit

Participants will be required to maintain a comprehensive food diary and collect one stool sample during the three days leading up to the visit. During the follow-up visit, the participant’s body weight will be measured again and they will fill in the self-reported questionnaires.

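### Controlling for BMI change, which arises after randomisation and is itself an outcome, does not estimate the total effect of SCFAs and can distort the estimate

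*Protocol article*

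**What the plan says.** The analysis section of the protocol article (Statistical methods for primary and secondary outcomes) first sets out a linear mixed model with group, visit (pre- or post-intervention) and, where relevant, timepoint. It names the group-by-visit and group-by-visit-by-timepoint interactions as the effects of main interest. Two sentences later it adds: "To investigate the effect of the SCFAs intervention on treatment response, we will further control for BMI". The means is to "control for BMI by including changes in BMI between visits 1, 2, and 3 in the linear mixed model as a continuous covariate".

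Other sections fix what kind of variable this is:

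- Study aims predicts "an improvement in the nutritional state, reflected by a greater increase in BMI" under SCFAs.
- Primary and secondary outcomes says "The primary outcome of this study focuses on the salivary cortisol response to acute laboratory stress", and lists BMI with food choice as the crucial secondary outcomes.
- Trier social stress test (TSST): "During the baseline and post-intervention visits, participants will complete the TSST". The choice phase of the food choice task follows the stress test at those same visits.
- Study design and setting places "a post-intervention visit at six weeks, and a follow-up visit at 12 weeks".
- At the follow-up visit, "body weight will be measured again and they will fill in the self-reported questionnaires"; a food diary and stool sample are also collected, but no stress test is held.

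**The concern.** Randomisation balances what exists at baseline. BMI change does not exist at baseline, so it cannot confound the comparison of groups and needs no control on that ground. By the protocol's own hypothesis it is a consequence of treatment. Conditioning on it can take out whatever part of the SCFA effect runs through weight gain. Where BMI change and the cortisol response share an unmeasured cause, such as illness severity, it also brings in a non-randomised association. The resulting coefficient is neither the total effect nor an identified direct effect, yet the article presents it as a way to study the intervention's effect.

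Timing adds a second problem. The visit 2-to-3 change accrues between weeks 6 and 12, after the last stress test and food choice task. It can neither cause nor confound those outcomes.

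At stake is which number is read as the SCFA effect if the unadjusted and adjusted models disagree.

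**Working it through.** **1. The plan's own power figure.** Sample size gives 40 per arm (N = 80), f = 0.16, a 2 × 2 within-between design and 80% power; alpha is 0.05. The correlation between visits (ρ) is not given, so ρ = 0.5 is assumed.

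- λ = f² × N × m / (1 − ρ) = 0.0256 × 80 × 2 / 0.5 = 8.192, with 1 and 78 degrees of freedom.
- Power = 0.807, and the f detectable at 80% power is 0.159. The stated figure reproduces.
- At other values of ρ, power is 0.516 (ρ = 0), 0.666 (0.3) and 0.954 (0.7).
- As a standardised difference in change scores: d = √(4λ/N) = √(4 × 8.192/80) = 0.64.

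**2. Does the coding matter?** A subject-level BMI change entered as a main effect has the same value at both visits, so it cancels from post minus pre. The check simulated 60 trials of 40 per arm with an assumed BMI shift of 0.5 SD and slope of 0.4, and fitted four mixed models:

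| BMI-change coding | Mean group-by-visit estimate |
|---|---|
| Not included | 0.677 |
| Main effect only | 0.677 |
| Interaction with visit | 0.461 |
| Time-varying | 0.463 |

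The first two agree to rounding error in every simulated trial. The drop in the last two, about 0.21 to 0.22, is close to the expected 0.5 × 0.4 = 0.20. The article specifies an interaction with visit for the SCFA-level covariate in the next sentence, but not for BMI.

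**3. Possible size where the coding bites.** Let SCFAs shift BMI change by *a* SD, and let the within-arm slope of the outcome on BMI change be *b*, signed so that this path runs in the same direction as the total effect. Adjustment then removes a × b. The documents give neither value, so both are assumptions.

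- a = 0.2: b = 0.2 removes 0.04/0.64 = 6%; b = 0.4 removes 0.08/0.64 = 13%.
- a = 0.5: b = 0.2 removes 0.10/0.64 = 16%; b = 0.4 removes 0.20/0.64 = 31%.
- The base effect also depends on ρ, since d = 0.16 × √(8/(1 − ρ)). At ρ = 0, d = 0.45 and the range is 9% to 44%. At ρ = 0.7, d = 0.83 and it is 5% to 24%.
- For power, a = 0.4 with b = 0.4 moves the simulated estimate from 0.64 to 0.48 and power from about 0.81 to 0.61.

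**4. No causal path, only a shared cause.** With an unmeasured cause loading 0.5 on both BMI change and the outcome, and a BMI shift of 0.4 SD, the induced slope is 0.5 × 0.5 = 0.25. The shift in the estimate is 0.25 × 0.4 = 0.10. Simulation agrees: 0.64 becomes 0.54.

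**5. SCFAs do not change BMI (a = 0).** The estimate stays at about 0.64 for every slope tried, so there is no bias.

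**The case against.** The strongest reply is that the decisive contrast is unadjusted. The group, visit and timepoint model comes first and its interactions are named as the main effects of interest; the word *further* then most naturally introduces an additional model. This largely stands. A reader might infer that the primary analysis itself is adjusted for BMI change and that part of the treatment effect is therefore lost, but the text does not support that. What remains is a second model, aimed at the intervention's effect, with no exploratory, mediation or sensitivity label. The same section does label its subtype and questionnaire analyses as explorative, and the article does not say which model decides if the two differ.

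Second, as literally written the covariate is a plain continuous term with no visit interaction, and in that form it leaves group-by-visit alone. This also stands, so distortion is conditional. But the term then fails to provide the control for which it was added.

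Third, *treatment response* is not tied to cortisol. Questionnaires are also completed at visit 3, where BMI from that visit is contemporaneous, and a time-varying coding would not set week-12 BMI against a week-6 outcome. The timing point therefore applies to cortisol and food choice. Against this, the model's visit factor has only the pre- and post-intervention levels.

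Two further inferences are tempting but not supported. One is that participants without a follow-up visit drop out of the model: no complete-case rule is stated, ward staff weigh participants repeatedly, and a follow-up visit is sought even after early departure. The other is that BMI as an outcome is adjusted for its own change: that would be circular, but the article does not say the covariate enters that model.

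**Conclusion.** The concern holds in a limited form. The article proposes to study the SCFA effect while conditioning on a post-randomisation variable that is itself a key outcome, is predicted to respond to treatment, and is partly measured after the last stress test. A group effect adjusted in this way is not the total effect and lacks the protection of randomisation.

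Actual distortion needs three things: SCFAs change BMI (as the protocol predicts), BMI change is related to the outcome causally or through a shared cause, and the covariate interacts with visit or varies over time. If the first or second fails there is no bias. If the third fails, group-by-visit is essentially unchanged and the intended control is not achieved.

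The 6% to 31% range is illustrative and should not be quoted as an expected loss; every input beyond f = 0.16 and N = 80 is assumed. The direction is not fixed either. Study aims predicts only that SCFAs will modulate the stress response, and a slope of the opposite sign would enlarge the estimate instead.

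**What to change.** State that inference on the SCFA effect rests on the group-by-visit and group-by-visit-by-timepoint terms from the model without any post-baseline BMI. Baseline BMI may be a covariate if wanted, but this point does not require it.

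If a BMI-change model is kept:

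- label it as exploratory mediation and say what it is meant to show;
- keep group in the model;
- use only the visit 1-to-2 change for outcomes measured at visit 2;
- state how the covariate is coded, including whether it interacts with visit;
- do not apply it to BMI as an outcome.

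The cost is a wording change in the analysis section, with no new data. It should be made before unblinding.

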### Measurements related to the TSST

#### Neuroendocrine measures

To measure the adrenocortical stress response during the TSST, we will collect eight saliva and four blood samples at regular intervals before, during, and after stress induction (see Fig. 3). Saliva samples will be obtained using synthetic Salivette devices and will be used to determine salivary cortisol and alpha-amylase (sAA) levels. Blood samples will be collected through an IV catheter in EDTA tubes to measure ACTH levels. After collection, all samples will be centrifuged and stored at − 80 °C until analysis by ELISA. Additionally, the participants' menstrual cycle phase and any use of hormonal contraceptives will be noted for its effect on the salivary cortisol response to acute stress.

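### As worded, the control for BMI leaves the cortisol interaction effects unchanged or nearly so, so it cannot show whether weight gain explains a cortisol effect

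*Protocol article*

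**What the plan says.** The statistical section analyses primary and secondary outcomes with linear mixed models containing group, visit (pre or post) and, where relevant, timepoint within visit. It states: "The group-by-visit and the group-by-visit-by-timepoint interaction effects constitute the principal effects of interest". To study treatment response it will then further "control for BMI by including changes in BMI between visits 1, 2, and 3 in the linear mixed model as a continuous covariate". The following sentence, on circulating SCFAs, enters the change in SCFA level "into the linear mixed model as a continuous covariate, including its interaction with visit, while omitting the group variable".

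The primary outcome is the salivary cortisol response to the stress test. The Trier social stress test section fixes when cortisol is available: "During the baseline and post-intervention visits, participants will complete the TSST". Under Neuroendocrine measures, "we will collect eight saliva and four blood samples at regular intervals before, during, and after stress induction". At week 12 the participant's "body weight will be measured again and they will fill in the self-reported questionnaires", and the Follow-up visit section mentions no stress test.

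The Study aims predict, under SCFA, "an improvement in the nutritional state, reflected by a greater increase in BMI". The Background describes nutritional deprivation as a possible driver of chronic HPA-axis stimulation.

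**The concern.** By the document's own account, weight gain is a rival explanation for a cortisol effect: SCFA is expected to raise BMI, and undernutrition is said to activate the stress axis. A step described as controlling for BMI should bear on that question.

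A change score does not vary over a participant's visits or saliva samples. Without an interaction it can explain only differences in participants' overall cortisol level. The effects of interest are differences within participants: post minus pre, and how that difference varies over the samples. The adjusted and unadjusted results would then agree whether weight gain explains everything or nothing. Anyone who took that agreement as evidence against renourishment would be relying on a model that did not test it.

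**Working it through.** **Inputs.** 40 participants per arm and 15% dropout (Sample size); two visits with cortisol and eight saliva samples per visit; the two principal interactions; BMI change as a covariate with no interaction named. The documents give no size for the BMI difference between arms or for its link with cortisol, so the simulation values below are assumptions.

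**1. The plan's own figure.** None concerns the BMI adjustment. The nearest is 80% power for the visit-by-treatment effect at f = 0.16. With lambda = f² × N × m / (1 - rho) = 0.0256 × 80 × 2 / 0.5 = 8.19 on 1 and 78 df, power is 80.7%. The correlation rho is not stated: 0.5 reproduces the figure, while 0.3 gives 66.6% and 0.7 gives 95.4%. This figure is not in dispute.

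**2. One change score, no interaction.** Let D_i be participant i's BMI change, with arms S (SCFA) and P (placebo), visits 1 and 2, and sample t. The model is Y_ivt = m_gvt + γD_i + error. Group, visit and timepoint are fully crossed, so with complete data the fitted cell value is (cell mean) - γ × (mean D in that arm), whatever the error covariance. The group-by-visit contrast at sample t is

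Δ_t = (m_S2t - m_S1t) - (m_P2t - m_P1t).

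The term γ × mean D appears at both visits within each arm and cancels. The three-way effect consists of differences Δ_t - Δ_s, so it is unchanged too. Adding a second score for visits 2 to 3 alters nothing, because it is also constant within participant.

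**3. BMI change coded by visit (zero at visit 1, D_i at visit 2).** Δ_t now shifts by -γ(mean D_S - mean D_P), by the same amount at every sample. Group-by-visit moves; Δ_t - Δ_s does not. The three-way effect moves only if γ may differ by sample, that is, with a timepoint interaction.

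**4. Numerical check.** One simulated complete trial: 40 per arm, 2 visits, 8 samples, mean BMI change 1.0 (placebo) and 2.2 (SCFA), SD 0.8. Treatment acts on cortisol (arbitrary units) only through BMI change, so a working adjustment should give values near zero, apart from sampling error. The models had random participant and participant-by-visit effects.

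| BMI change in model | Group-by-visit, averaged (z) | Three-way, peak vs first sample | Three-way Wald/7 |
|---|---|---|---|
| none | -0.383 (-2.03) | -0.712 | 3.40 |
| one score, no interaction | -0.383 (-2.03) | -0.712 | 3.40 |
| coded by visit, zero at baseline | +0.320 (1.96) | -0.712 | 3.40 |
| score × visit | +0.303 (1.84) | -0.712 | 3.40 |
| score × visit × timepoint | +0.303 (1.84) | +0.282 | 1.40 |

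In a trial with 15% of participants lacking visit 2, the score without interaction moved group-by-visit from -0.692 to -0.678, a shift of 0.014 or about 2% (0.014/0.692). The three-way effect stayed at -1.165. With all interactions the two became +0.117 and +0.008.

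**5. Repetition.** Over 60 simulated complete trials (BMI change 1 SD higher under SCFA), the mean group-by-visit estimate was -0.257 without BMI, -0.257 with the score alone (largest difference 2e-15) and +0.008 with score × visit. Generalised least squares on 50 and on 30 further complete trials, with arbitrary 16 × 16 covariances, left both principal effects unchanged to about 1e-13. Coding by visit moved group-by-visit by up to 0.63 and never moved the three-way effect.

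**The case against.** The algebra is not open to dispute, but the reading of the sentence is. The article does not say that BMI change enters only as a main effect; that is inferred from the absence of an interaction. The contrast with the SCFA sentence is also weaker than it looks. There the group term is dropped, so the visit interaction is itself the test and has to be named. The later sentence on questionnaire changes names no interaction either, so silence may be shorthand in a condensed article. The plural wording about changes across three visits could mean a visit-indexed covariate, and the sentence is not confined to cortisol.

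Much of this stands. A reader might infer that BMI change cannot alter group-by-visit under any coding. The documents do not support that, since coding by visit would move it. A reader might also infer that the trial will report a cortisol effect as independent of weight gain. No section says so; that is a prediction about the report.

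Two things remain. A visit-indexed covariate is not described, and for cortisol the change from visit 2 to visit 3 has no observations of its own to attach to. And even under the favourable coding the three-way effect does not respond, although it is the effect that describes the response to stress. The article states the form of the covariate, and following that form gives an adjustment that does not adjust, so this goes beyond detail left to an analysis plan.

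**Conclusion.** The point holds with limits. On the plain reading, the change in both principal effects from controlling for BMI is exactly zero with complete data. It is small when visits are missing (0.014 against -0.692 in the simulated trial with 15% missing). If single samples rather than whole visits are missing, invariance of the three-way effect is also only approximate. Under coding by visit, the criticism applies to the three-way effect alone.

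The exact result rests on algebra and not on the assumed effect sizes. The simulated magnitudes show what the codings do and say nothing about how large the effect will be in this trial. The unadjusted randomised comparison is not biased by any of this; the defect is a supplementary model that cannot answer the question put to it. The wording should be corrected, but the trial's principal analysis does not depend on it.

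**What to change.** In Statistical methods for primary and secondary outcomes, replace the BMI sentence, for cortisol, by one of two forms:

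- BMI change from baseline to week 6, with its interactions with visit and with visit-by-timepoint; or
- BMI at each visit as a time-varying covariate, with its interaction with timepoint.

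Drop the visit 2-to-3 change from the cortisol model, since cortisol is not measured at visit 3. If another coding was intended, state it; a timepoint interaction is needed either way.

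Present this model as supplementary and exploratory beside the unadjusted comparison. BMI change arises after randomisation and is itself a hypothesised treatment effect, so the adjusted estimate no longer has the protection of randomisation. Make no claim that a cortisol effect is independent of BMI from a model without these interactions.

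The cost is one or two sentences and a larger supplementary model. With timepoint as an eight-level factor, the first form adds 1 + 7 + 7 = 15 coefficients to the single covariate. The interval may widen, especially if BMI change differs by arm but predicts cortisol weakly. In the complete simulated trial, where BMI change was strongly predictive by construction, the group-by-visit standard error went from 0.189 to 0.165. No new data are needed.
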